**Treatment failure:**

Treatment failure is defined by the persistence of danger signs of severe pneumonia for >48 hours or deterioration within 24 hours of initiation of therapy or if child needs mechanical ventilation, dies at any time during hospital stay or left the hospital against medical advice.

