**Secondary objectives:**

To compare time to resolution of danger signs of pneumonia, length of hospital stay, mortality rate, rate of complication requiring mechanical ventilation, and rate of multiorgan or renal or cardiac failure between the two treatment groups.

**Primary Outcome:** Treatment failure which is defined by the persistence of danger signs of severe pneumonia for >48 hours or deterioration within 24 hours of initiation of therapy (development of new danger signs or clinical signs of respiratory failure, or development of severe sepsis/meningitis, or, radiological deterioration).

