### *Inclusion criteria:*

Children more than 2 months to less than 59 months will be enrolled in our study, if they have a history of cough or difficulty in breathing and WHO classified severe pneumonia plus **at least two of the following:**

- i) Central cyanosis or oxygen saturation <90% on pulse oxymetry
- ii) Severe respiratory distress (e.g. grunting, very severe chest indrawing)
- iii) Signs of pneumonia with a general danger sign: inability to breastfeed or drink; lethargy or reduced level of consciousness; convulsion
- iv) In addition, some or all of the other signs of pneumonia may be present, such as:
  - Signs of pneumonia [age specific fast breathing( *Annex I*)]
  - Chest indrawing: lower chest wall indrawing
  - Chest auscultation signs: (any one)
    - a) Decreased breath sounds
    - b) Bronchial breath sounds
    - c) Crackles
    - d) Abnormal vocal resonance (decreased over a pleural effusion or empyema, increased over lobar consolidation)
    - e) Pleural rub

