### **Study Interventions:**

Children between 2 months to 59 months with severe pneumonia will be studied to evaluate the proportions of treatment failure in two different arms.

We will use sealed envelopes to randomly assign the children to either treatment arms. In first arm children will receive 2 daily doses of parenteral Amoxicillin and single daily dose of parenteral Gentamicin; and in 2nd arm, children will receive 4 daily doses of parenteral Ampicillin and single daily dose of parenteral Gentamicin. After 72 hours of treatment, injection Amoxicillin and injection Ampicillin will be replaced with oral Amoxicillin but injection gentamicin will be continued for total 5 days in once daily dose. During this time patient will be suggested to discharge from hospital and attend to Ambulatory care unit for getting once daily dose of injection Gentamicin. Both the treatment arm will continue for 5 days.

During the study period, children in both study arms will also receive standardized hospital management for diarrhoea and malnutrition (*Annex 2,3*).

“Treatment failure” will be standardized, based on clinical and monitoring data. Treatment failure is defined by the persistence of danger signs of severe pneumonia for >48 hours or deterioration within 24 hours of initiation of therapy or if child needs mechanical ventilation, dies at any time during hospital stay or left the hospital against medical advice.

During the study period any child from either study group who develops the features of “clinical failure” (any two of three criteria in the definition below) will be managed according to best practice in the clinical context. If children fail any arm of treatment, they should be rescued with second line antibiotic regimen, which is injection ceftriaxone and injection levofloxacin. Hypoxia will be managed by B-CPAP or humidified high flow air / O2 mix at 2 l/kg/min through nasal cannula.

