### **Monitoring of the children with severe pneumonia**

The following parameters should be routinely monitored in every child with severe pneumonia. Special attention should be given to child receiving I/V fluid therapy and those with SAM. Such as: Heart rate, respiratory rate, temperature, respiratory pattern including chest recession, lower chest wall in drawing, use of accessory muscles, establishment of oral feeding, liver size, oxygen saturation level, chest auscultation: (rales, rhonchi, bilateral basal crepitation, pleural rub), fluid and calorie intake.

Children on oxygen therapy should have at least 3-4 hourly observations of all the above parameters and children without getting oxygen should be observed at least 2 hourly by the study nurses. All the patients should be evaluated by the physicians at least 12 hourly by the physicians.

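### The failure definition does not count a change of antibacterial, so a child who worsens after 24 hours, or who entered without a danger sign and does not respond, can be switched, recover and be scored a success

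*Protocol*

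**What the plan says.** Failure is described in five places: the Project Summary (Treatment failure), Specific Aims (Primary Outcome), Study Interventions, the sample size section (Primary Outcome), and the list under Intention to treat (ITT) analysis.

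- The core, common to the first four, is "persistence of danger signs of severe pneumonia for >48 hours or deterioration within 24 hours of initiation of therapy".
- Specific Aims and the sample size section spell out what deterioration means: "development of new danger signs or clinical signs of respiratory failure, or development of severe sepsis/meningitis, or, radiological deterioration". This stays tied to the first 24 hours.
- The Project Summary, Study Interventions and the ITT list add mechanical ventilation, death in hospital and leaving against medical advice. In Study Interventions the wording is "deterioration within 24 hours of initiation of therapy or if child needs mechanical ventilation, dies at any time during hospital stay".
- The Project Summary lists three danger signs: inability to feed or drink, lethargy or reduced consciousness, and convulsions.
- The inclusion criteria ask for at least two listed features. The first is "Central cyanosis or oxygen saturation <90% on pulse oxymetry" and the second is severe respiratory distress, so these two together are enough.

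On changes of treatment, Study Interventions has two adjacent sentences. A child with clinical failure ("any two of three criteria in the definition below") "will be managed according to best practice in the clinical context". For children who fail an arm, "they should be rescued with second line antibiotic regimen, which is injection ceftriaxone and injection levofloxacin". No list of three criteria follows anywhere in the protocol. Hypoxia is to be managed with bubble CPAP or high-flow air and oxygen.

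On review, "All the patients should be evaluated by the physicians at least 12 hourly by the physicians". CRF item 141 records antibiotics with start and stop dates and a comment. CRF item 153 asks only whether treatment failure occurred.

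**The concern.** The hypothesis is about failure with the assigned regimen. A child whose illness prompted a change to other antibacterials, and who then recovered on them, says little in favour of that regimen. Under every version of the definition that child can still be a success.

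This matters more in a non-inferiority trial than in a superiority trial. If the same share of failures is masked in each arm, a true excess of failures on amoxicillin shrinks towards zero, which helps the non-inferiority claim.

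**Working it through.** **Can a switched child avoid every component?**

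1. *Deterioration after 24 hours.* With physician review every 12 hours, the reviews at 36, 48, 60 and 72 hours all fall outside the 24-hour window but within parenteral treatment. Respiratory failure signs, severe sepsis or meningitis, or radiological worsening first seen then meet no component unless the child is ventilated, dies or leaves. A new danger sign at 36 hours counts only if it then satisfies the 48-hour persistence rule. If a switch clears it in time, it does not.
2. *No danger sign at entry.* A child admitted on hypoxaemia plus severe respiratory distress has no danger sign that could persist, unless a new one appears. CRF item 149 allows for this by adding an if-any qualifier to the duration of danger signs. If such a child stays hypoxaemic, is switched and recovers, no component is met.

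**The plan's own sample size.** Inputs from the sample size section: failure proportion 0.50 in both arms, margin 0.16, one-sided alpha 0.025, power 0.80.

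n per arm = (1.960 + 0.842)² × 2 × 0.5 × 0.5 / 0.16² = 153.3, rounded up to 154 (308 in total). The stated figure is reproduced.

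**Effect of masking (illustration).** The protocol gives no switch rate, so the masked share s is an assumption. Take true rates of 0.58 (amoxicillin) and 0.42 (ampicillin), which put the difference at the margin.

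- SE = √(2 × 0.5 × 0.5 / 154) = 0.05698.
- The observed difference is 0.16(1 − s).
- P(claim non-inferiority) = Φ(0.16 s / SE − 1.96).
- Children masked are 154 × 0.58 × s and 154 × 0.42 × s.

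| s | Masked, amoxicillin / ampicillin | False claim |
|---|---|---|
| 0 | 0 / 0 | 2.5% |
| 1% | 0.9 / 0.6 | 2.7% |
| 2% | 1.8 / 1.3 | 2.8% |
| 5% | 4.5 / 3.2 | 3.4% |
| 10% | 8.9 / 6.5 | 4.7% |

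Recomputing SE at the reduced rates gives 3.5% at s = 5% and 4.7% at s = 10%. Simulation of 2 million trials with a Wald limit gives 2.4%, 2.6%, 2.8%, 3.4% and 4.5% down the table. If the same number of children is masked in each arm, the difference stays at 0.16 and the false-claim rate stays at 2.5%.

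**Power cost of counting switches.** Suppose both true rates are 0.50 and open-label clinicians add k unwarranted failures in the amoxicillin arm only. Power = Φ((0.16 − k/154) / SE − 1.96):

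- k = 0: Φ(0.848) = 80%
- k = 1: Φ(0.734) = 77%
- k = 3: Φ(0.506) = 69%

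**The case against.** The strongest reply is that Study Interventions reserves ceftriaxone and levofloxacin for children who fail, so every switched child is already a failure. It adds that the best-practice sentence names no antibiotic, and that hypoxia is to be treated with respiratory support. This stands as a statement of intent, and nothing in the protocol suggests that switching without failure would be common. But the best-practice sentence uses a different trigger with no definition and sets no limit on drugs, and no sentence scores a switched child as a failure.

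A second reply is that the root defects are the 24-hour window and the narrow list of danger signs. That is fair. Counting switches does not capture a child who worsens at 36 hours and is left on the assigned drugs. It closes only the route by which a changed treatment earns credit for the assigned one.

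A third reply is that rescue handling can be left to a statistical analysis plan. Here, however, the protocol itself states the endpoint rule, and that rule is what misclassifies the child.

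Three stronger readings are tempting and should not be drawn:

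- *Switches could not be found afterwards.* Item 141 has rows for the main non-assigned drugs, with dates and a comment column, so most such use would be visible. Only clock time, a coded reason and an open row are missing.
- *Children are checked at 48 hours and switched if unimproved.* Signs of Improvement describes what to expect within two days. It schedules no assessment and attaches no decision.
- *The daily CRF signs already document the reason for a switch.* Items 112 to 135 use an SpO2 cut-off of 85% and have no fields for feeding, consciousness, convulsions, sepsis or meningitis. The single chest X-ray item (140) carries no date.

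**Conclusion.** The gap in the definition is real and can be read directly from the text. Its consequence is minor to moderate and of unknown size.

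The illustration assumes a true difference exactly at the margin and the same share of failures masked in both arms. On those assumptions the effect is small up to 5% masked (2.5% to about 3.4%) and modest at 10% (about 4.7%). With equal numbers masked there is none. A reader might infer that a non-inferiority result from this trial would be invalid. The documents do not support that, because they give no switch rate and intend second-line drugs for failures.

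The protocol should still be changed: the rule can credit a regimen with recoveries achieved on other drugs, and the correction is cheap.

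**What to change.** 1. Add one component to every version of the definition: *or start, during the 5-day study regimen, of any systemic antibacterial other than the assigned regimen (including its planned oral amoxicillin step-down) for pneumonia, sepsis or non-response*. Exempt treatment of dysentery, cholera or another separate infection.
2. In Study Interventions, replace clinical failure and its two-of-three rule with treatment failure, so that rescue and endpoint follow the same rule.
3. In CRF item 141, add a start time, a coded reason and an open row for any other antibacterial.
4. Report non-assigned antibacterial use by arm, and give the primary result with and without the new component as a sensitivity analysis.

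**Cost.** One clause, one replaced term, three CRF additions and one table. The sample size does not grow, because planning at 0.50 already uses the largest binomial variance. The downside is that the component depends on clinicians who know the allocation. Extra switches in the amoxicillin arm would be conservative for non-inferiority but would cost the power shown in the working. The analysis without the component shows how much the result depends on it.

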### **Monitoring of the children with severe pneumonia**

The following parameters should be routinely monitored in every child with severe pneumonia. Special attention should be given to child receiving I/V fluid therapy and those with SAM. Such as: Heart rate, respiratory rate, temperature, respiratory pattern including chest recession, lower chest wall in drawing, use of accessory muscles, establishment of oral feeding, liver size, oxygen saturation level, chest auscultation: (rales, rhonchi, bilateral basal crepitation, pleural rub), fluid and calorie intake.

Children on oxygen therapy should have at least 3-4 hourly observations of all the above parameters and children without getting oxygen should be observed at least 2 hourly by the study nurses. All the patients should be evaluated by the physicians at least 12 hourly by the physicians.

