### **Respiratory ward Infrastructure:**

An independent acute respiratory infection treatment unit was established right at the entrance to the hospital, and started functioning on 6 September, 2009. Patients reporting to Dhaka Hospital were rapidly screened for

respiratory symptoms such as fever, cough, myalgia, headache, chills, fatigue, running nose, sore throat, rapid breathing and difficulty in breathing. Patients with these symptoms were referred to the respiratory triage where they were assessed following the hospital guidelines and relevant information was entered into the hospital's electronic database. Patients with any form of pneumonia (non-severe, severe, and very severe), bronchiolitis, asthma, bronchitis, pleural effusion, empyema, lung abscess, tuberculosis, and any other common respiratory problems are admitted in the ward. Others were referred to the usual diarrhoea triage of the hospital. Sufficient staff provide 24 hour cover from all cadres (doctors, nurses, health workers and auxiliary staff). This facility was provided with all necessary supplies including a portable X-ray machine, Ambu bags, large oxygen cylinders, pulse oxymeters, disposable gloves, disinfectants and medication (e.g. antibiotics and other medicines). Pulse oxymetry is routinely performed to evaluate arterial oxygen saturation, and additional tests were performed if there were clinical indications. Vital signs were monitored, and stool and urine output was measured and recorded 8 hourly. Therapy is decided on the basis of clinical evaluation, results of the laboratory tests, and the hospital guidelines for management of respective respiratory illness.

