### **Collection of Baseline Information**

- All children within the defined age group suspected to have ALRI will be screened for study eligibility. Parents/ attending care givers of those fulfilling the eligibility, in application of the inclusion and the exclusion criteria, will be invited to provide their consent for enrollment of their children in the study. Upon signing a written informed consent, after providing information about the study and its interventions, possible benefits and risks, and voluntary nature of participation along with the right to withdraw children at any time after the initial consent without providing any reason, children will be enrolled. Case Record Form (CRF, ANNEXURE 1) will be used to collect relevant information such as medical history including nature and duration of illness, medication for current illness; socio-demographic characteristics such as sex, religion, parental age with education, parents occupation and smoking history, monthly family income, number of siblings, number of rooms, and cooking in bed room. Information will also be collected about child’s feeding practice such as history of breast feeding, formula or other complementary feeding, and immunisation status; family history of tuberculosis, recent respiratory tract infection of any family members and past history of child’s pneumonia, and history of exposure of the child to sun would be recorded. Examination findings to be recorded include pulse and respiratory rate, axillary temperature, anthropometric measurement, chest auscultation findings, chest wall in drawing, oxygen saturation, presence of cyanosis, and mental status (normal, irritable, lethargic). Weight of each child will be measured by electronic weighing scale with a precision of 0.1 kg and height/length will be measured using a locally made length board with precision of 0.1cm. Fever will be defined when the axillary temperature is 38°C or greater. Respiratory rate will be counted for full 60 seconds by exposing the trunk when the child is awake and calm, and presence of lower chest wall in drawing will be noted at the same time. Respiratory rate will be counted for two times and if they differ by more than 5 breaths per minute then a third reading will be made, and the average of two closest respiratory rates (not deviating by 5 or greater number) will be regarded as the actual rate. Oxygen saturation will be measured using a Pulse Oxymeter (Nellcor Puritan Bennett Inc. N-560, Made in Korea) with a probe on a finger or toe when the child breathes in room air. Oxygen saturation of 90% or lesser will be defined as hypoxia which will be the indication for oxygen therapy. If the child is sick we may require taking 5 mL of blood sample (approximately 1 tea spoon full) according to usual hospital management protocol.

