|------------------------|-----------------------------------------------------------------------------------------------------------------------------------------------------------------------------------------------------------------------------------------------------------------------------------------------------------------------------------------------------------------------------------------------------------------------------------------------------------------------------------------------------------------------------------------------------------------------------------------------------------------------------------------------------------------------------------------------------------------------------------------------------------------------------------------------------------------------------------------------------------------------------------------------------------------------------------------------------------------------------------------------------------------------------------------------------------------------------|
| Human resource         | 
Project Research Physicians (PRP): ( 100% FTE, 1 persons; US\$ 7,112 salary) One physician will be assigned from 8:30-5 PM (6 days a week) for 12 months for screening and enrolment of the patient. Additionally, he/she will co-ordinate with all clinical activities including obtaining medical history, consents, performing clinical assessment, and prescribing treatment to enrolled patients.
 
Study Nurse (SN): ) (100% FTE, 4 SN, US\$ 17,780 salary): Four nurses will be recruited to cover the 24 hours duties in the whole study period. Nurses will be responsible for taking routine clinical care of study patients and monitor the vital signs on enrolment and 8 hourly.
 
Health Workers (HW) (100% FTE, 2 HW, US\$ 7,493 salary): Two HW will be recruited for the whole study period. HWs will be responsible for subject selection and motivation. HWs will be responsible for collection, prompt transportation of sample from ward to laboratory (if required), escorting patient for radiology tests etc.
 |

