## SECTION 2: CLINICAL INFORMATION

In days

43. Symptoms:

Fever

1= yes, 2= no

☐

for how long? \_\_\_\_\_

☐

Cough

1= yes, 2= no

☐

for how long? \_\_\_\_\_

Nasal discharge

1= yes, 2= no

☐

for how long? \_\_\_\_\_

Diarrhoea

1= yes, 2= no

☐

for how long? \_\_\_\_\_ If yes, Clinical

types of diarrhea

1=AWD, 2=ID, 3=PD

☐

Dehydration

1= yes, 2= no

☐

Clinical types of dehydration on admission

1=no sign, 2= some, 3= severe

☐

Vomiting

1= yes, 2= no

☐

for how long? \_\_\_\_\_

Poor feeding

1= yes, 2= no

☐

for how long? \_\_\_\_\_

Difficulty in breathing

1= yes, 2= no

☐

for how long? \_\_\_\_\_

Oedema

1= yes, 2= no

☐

for how long? \_\_\_\_\_

Irritable

1= yes, 2= no

☐

for how long? \_\_\_\_\_

Rash

1= yes, 2= no

☐

for how long? \_\_\_\_\_

☐

Convulsions 1= yes, 2= no for how long? \_\_\_\_\_

Number of episodes of convulsion prior to admission

Number of episodes of convulsion after admission

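### The stated minimum nurse-observation interval is longer for children on oxygen (3-4 h) than for children off oxygen (2 h)

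*Protocol*

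**What the plan says.** The Protocol section Monitoring of the children with severe pneumonia lists the parameters to be followed in every child and then sets two nursing minima:

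- On oxygen: "Children on oxygen therapy should have at least 3-4 hourly observations of all the above parameters".
- Off oxygen: "children without getting oxygen should be observed at least 2 hourly by the study nurses".

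Physician review is at least every 12 hours for all children, whatever their oxygen status.

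Two other sections show who is on oxygen. Collection of Baseline Information states: "Oxygen saturation of 90% or lesser will be defined as hypoxia which will be the indication for oxygen therapy". Study Interventions adds: "Hypoxia will be managed by B-CPAP or humidified high flow air". That second sentence stands in the paragraph on children who fail treatment, and the case record form also lists standard nasal prongs as a route. Children on oxygen are therefore hypoxic by definition, and some of them will be on CPAP or high flow.

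Two other places give a recording interval. Budget Justifications has the study nurses "monitor the vital signs on enrolment and 8 hourly". Respiratory ward Infrastructure says of the ward: "Vital signs were monitored, and stool and urine output was measured and recorded 8 hourly".

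**The concern.** A child who needs respiratory support is more likely to deteriorate quickly than one who does not, so one expects the shorter interval on oxygen. The text gives the reverse. Because each interval is a minimum, it defines what counts as compliant care: a nurse could leave a child on CPAP or high flow unobserved for up to 4 hours and still meet the protocol, whereas a child breathing room air must be seen every 2 hours.

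What is at stake is mainly the safety of the hypoxic children, who are central to this trial because low saturation or cyanosis is one of its entry criteria.

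**Working it through.** **The plan's calculated figure.** The Protocol's only calculated design figure is the sample size. With p = 0.50 in both groups, a margin of 0.16, one-sided alpha 0.025 and power 0.80:

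n = (1.960 + 0.842)² × (0.25 + 0.25) / 0.16² = 7.85 × 0.5 / 0.0256 = 153.3, rounded up to 154 per group and 308 in total.

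This reproduces the stated figure, and no observation interval enters it.

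**Inputs for this point.** On oxygen: every 3-4 h. Off oxygen: every 2 h. Both come from the monitoring section. The 8-hourly duty comes from Budget Justifications.

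**Required observations per 24 h** (24 / interval):

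- On oxygen: 24/4 = 6 to 24/3 = 8
- Off oxygen: 24/2 = 12
- Budget text: 24/8 = 3

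**Longest compliant gap.** Difference: 3 − 2 = 1 h to 4 − 2 = 2 h longer on oxygen. Ratio: 3/2 = 1.5 to 4/2 = 2.

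**Does another section give children on oxygen a shorter interval?**

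- Physician review is every 12 h for everyone.
- The ward description offers 24-hour cover and routine pulse oximetry. Its only interval is 8 hours, which may apply to stool and urine output alone.
- The sections on laboratory investigations and on data safety monitoring refer to the hospital guideline and to standard operating procedures, without stating an interval.
- The intensive care unit is mentioned without an observation interval.

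No shorter interval is stated anywhere in the Protocol.

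**Workload of a 2-hourly minimum for all.** On oxygen the count rises to 12 per 24 h, so 12 − 8 = 4 to 12 − 6 = 6 are added per child-day. This assumes that each full assessment falls on a 2-hourly round and counts as that round. A strict 3-hourly full assessment coincides with the 2-hourly rounds only every 6 h, that is 4 times a day, so it would need 12 + 8 − 4 = 16 contacts, an addition of 8.

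**Illustrative total.** The Protocol gives neither the share of children on oxygen nor the length of stay. Assume 20-80% on oxygen, 3-5 days in hospital, and 308 children spread evenly over 12 months.

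- Study children in hospital at a time: 308 × 3/365 = 2.5 to 308 × 5/365 = 4.2
- Added observations per study child-day: 0.2 × 4 = 0.8 at the low end, 0.8 × 6 = 4.8 at the high end
- Added per day in total: 2.5 × 0.8 = 2 to 4.2 × 4.8 = 20

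The range is wide because both inputs are assumed.

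**The case against.** **The two checks may differ in content.** The on-oxygen check takes in every listed parameter, including auscultation, liver size, and fluid and calorie intake; the off-oxygen clause says only that the child is observed. A fuller check less often and a lighter one more often could be a reasonable scheme. This stands in part. A reader might infer that hypoxic children are monitored less overall, and the text does not support that: only the interval can be compared. But the text defines no lighter check, introduces the list as applying to every child, and gives a child on oxygen no 2-hourly check of any kind.

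**The figures are minima, and care will exceed them.** Physician rounds, 24-hour cover, routine oximetry, access to intensive care and the hospital's own procedures all make harm less likely. This also stands. It limits the likely consequence without correcting the sentence, because the minimum is what the protocol requires.

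**The 8-hourly statements are weak evidence.** The ward sentence is a past-tense description whose interval may belong to stool and urine output. It should not be read as an 8-hourly vital-signs rule. The budget line does name vital signs, but it is a staffing justification. It is worth making consistent and carries little weight by itself.

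**Conclusion.** The point holds for the interval. As written, the longest permitted gap between nurse observations is 1-2 h longer for children on oxygen than for those off it (3-4 h against 2 h), and no other section shortens it. This rests on reading each figure as a compliance minimum and on the Protocol's own rule that oxygen is given for hypoxia. The two figures may simply have been transposed; the document does not say. The wording should be corrected, although the existing cover makes the likely harm limited.

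Two stronger readings are not supported:

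- **Bias or loss of power.** A reader might infer that the primary outcome is distorted. The rule is the same in both arms, no misclassification rate can be derived, and the sample size does not depend on it.
- **An unverifiable 24-hour failure component.** That component includes "development of new danger signs or clinical signs of respiratory failure", and the case record form has an untimed entry, "Number of episodes of convulsion after admission". A reader might infer that the 24-hour window cannot be checked. But Study Interventions bases failure on clinical and monitoring data, not on the form alone, and items 147-149 are recorded in hours, which presupposes a start time in the source record. No wrong result is shown. Extra clock-time fields would be an optional refinement and form no part of this point.

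**What to change.** Replace the two nursing minima in the monitoring section with one rule. Suggested sense: a study nurse sees every child at intervals of no more than 2 hours and records at least respiratory rate, oxygen saturation, respiratory pattern and level of consciousness; a child on oxygen also has the complete parameter list assessed every 3-4 hours. This raises only the on-oxygen minimum, leaves the 2-hour minimum off oxygen in place, and says what the short check contains.

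If the investigators confirm that the intervals were transposed, swapping them is enough: 12 per 24 h on oxygen and 6-8 off it.

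In either case, amend the nurse-duty line in Budget Justifications so that it no longer implies 8-hourly vital signs.

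Cost: one sentence and one editorial line. The first option adds 4-6 brief observations per child-day on oxygen if full assessments are timed to the 2-hourly rounds, shared by the four study nurses already budgeted to cover 24 hours. A swap adds the same number on oxygen and removes the same number off it. Neither option changes the sample size or the analysis.
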